#### Secondary outcomes

2.3.4

There are ten secondary endpoints, defined as follows: 1) Feasibility and safety of TDM, measured as percentage of successful TDM interventions, in which successful is defined as target attainment with manageable toxicity; 2) ORR, defined as partial response or complete response (according to RECIST v1.1) percentage of the total treated population; 3) mOS, where OS is defined as time from randomization to death from any cause in the total population. Patients who do not die or are lost to follow-up will be censored at their last available date; 4) Intracranial PFS, defined as time from start of treatment to PD in the brain or death from any cause, whichever comes first. Patients not experiencing any of these events will be censored at their last available date; 5) Physician adherence to TDM advice, measured as the percentage of dose recommendations that are implemented by the treating physicians; 6) Patients’ medication adherence, estimated by pill counts of returned medication as well as a patient diary on drug intake; 7) Toxicity related to the plasma concentration and dose increases, defined as adverse events (AEs) in the subgroup with C_min,SS _< 435 ng/mL and all C_min,SS_ ≥ 435 ng/mL, and in patients who did and who did not receive a PK-guided dose increase; 8) QoL; this will be determined using the EORTC QLQ_LC13 as addition to the QLQ-C30 questionnaire, and the EQ-5D-5L questionnaire. 9) Cost-effectiveness, this will be determined from both a healthcare and a societal perspective. Costs associated with healthcare resource use in combination with Quality adjusted-life years will be used to determine an incremental cost-effectiveness ratio (ICER); 10) Alectinib-M4 concentrations, which will be measured in the alectinib plasma samples. For the endpoints regarding ORR, mOS, intracranial PFS, the comparison will be made between arm A and B, among patients who had a C_min,SS _< 435 ng/mL at any point during treatment. Feasibility and safety of TDM and physician adherence to TDM advice will only be evaluated in arm A. Patients medication adherence, toxicity, QoL, cost-effectiveness and alectinib-M4 concentrations will be evaluated in all patients.

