#### Intervention and control group

2.2.1

For patients in arm A (TDM group) plasma trough concentrations of alectinib will be analyzed directly from the PK samples. Results will be available within 1-2 weeks. In case of C_min,SS_ below the threshold of 435 ng/mL (in arm A) and no or limited toxicity, the patient receives a dose increase with 150 mg BID to a maximum of 900 mg BID. The dose levels are shown in **Table 1**. Four weeks after a dose increase, an extra PK sample is drawn to check whether the intervention was successful, i.e. when TDM target is reached with acceptable tolerability. When patients have adequate exposure (C_min,SS_ ≥ 435 ng/mL), the dose will be continued given no or acceptable toxicity. For patients in arm B, PK samples will be drawn conform the same schedule as patients in arm A. However, these samples will remain blinded to the patients and the treating physician until the end of the study. In case of unmanageable toxicity in both arms (i.e. unbearable or persistent grade 2 toxicity, or grade 3/4 toxicity according to Common Terminology Criteria for Adverse Events (CTCAE) v5.0), the alectinib dose can be reduced by one dose level (150 mg BID) in accordance with standard care unto a minimum of 300 mg BID. Temporary dose interruptions are allowed. If the side effects subside or are no longer present, it is allowed to increase the dose again. To estimate the C_min,SS_ of alectinib, the time of blood draw will be recorded and all patients will keep a paper diary to collect date and time of last intake of alectinib. Alectinib C_min,SS_ will be calculated with the following formula:

**Table 1 T1:** dose levels of alectinib.

Dose level	Alectinib Dose
-2	300 mg BID
-1	450 mg BID
0	600 mg BID
+1	750 mg BID
+2	900 mg BID

$$C_{min,SS}=\;C_{measured}*0.5^{\frac{dosing\;interval-TAD}{t_{1/2}}}$$

Where C_min,SS_ is the estimated minimum plasma concentration, C_measured_ the measured plasma concentration, the dosing interval is the time between two subsequent administrations, TAD is time after dose and t_1/2_ is the elimination half-life of the drug (i.e. 32 hours for alectinib). PK samples should be drawn after at least 4 hours after the last intake of alectinib (after T_max_) (16). It is assumed that this algorithm should perform equivalently, and most likely even better, as imatinib validated by Wang et al, since the half-life of alectinib is longer (16).

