#### Sample size calculation

2.3.2

It is expected that 48% of the patients treated with alectinib in our study will be underdosed (i.e. C_min_ < 435 ng/mL at a certain timepoint) based on the dataset of Groenland et al. (13). The observed mPFS for these patients was 12.6 months (95% confidence interval (CI): 9.2 months – not yet reached), which will serve as the assumed median in the subgroup with low exposure in the fixed-dosing group (arm B). The mPFS in the patients with C_min_ ≥ 435 ng/mL had not yet been reached (95% CI: 19.8 months – not yet reached) at the time of analysis, but the HR for the group with C_min_ < 435 ng/mL versus C_min_ ≥ 435 ng/mL was estimated as 2.5 (13). We expect that TDM-guided dosing can improve PFS in 67% of patients with a low exposure, to the extent that they obtain a similar outcome as patients with C_min_ ≥ 435 ng/mL. In this group, a HR (fixed versus TDM-guided dosing) of 2.5 is assumed. In the remaining 33% of patients, TDM-guided dose increases are expected not to be feasible due to toxicity or treatment discontinuation as a consequence of progressive disease (PD), so a HR equal to one is assumed for this subgroup. Altogether, this would result in an expected HR (fixed versus TDM-guided) of 2.0. With 67 events, a power of 80% will be obtained to detect this HR of 2 using the log-rank test and assuming a two-sided significance level of 5%. This translates into an improvement in mPFS from 12.6 months without using TDM-guided dosing to 25.2 months using TDM-guided dosing. Assuming an uniform patient accrual during 48 months and 12 months follow-up after inclusion of the last patient (total study duration of 60 months), 94 patients (47 per group) with C_min _< 435 ng/mL will need to be included for the primary analysis. Since 48% of the patients in the study are expected to have C_min _< 435 ng/mL at a certain timepoint, 196 patients will need to be recruited (13). Dropouts are expected to be kept to a minimum and it does occur, it is expected to be in the first 12 weeks, when substitution is still allowed. Dropouts are therefore not taken into account.

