### Data analysis

2.4

Survival endpoints will be analyzed using Kaplan-Meier curves and differences between groups will be tested using the stratified log rank test. The HR and its corresponding 95% CI from a stratified Cox model will be estimated. The median survival will be presented by arm along with 95% confidence intervals using the Brookmeyer and Crowley method. A p-value < 0.05 will be deemed statistically significant.

The effect of biomarkers in the secondary and exploratory study parameters (such as sequencing profile by AVENIO of biopsy) will be explored by correlating the changes in a marker to any outcome (such as OS). This will be performed by crosstabs, t-tests, Mann-Whitney U tests, and Spearman’s rank correlations, depending on the distribution of the data.

ORR will be calculated by arm with exact 95% CI. For comparing response rates in the two-treatment arms accounting for randomization stratification factors, the Cochran-Mantel-Haenszel test will be used at a two-sided 5% level of significance.

For treatment-emergent AEs (i.e., those starting or worsening during the period on treatment) summary tables will be provided by treatment group. Worst-grade AEs will be summarized by system organ class and preferred term, severity (by CTCAE v5.0 criteria) and relation to study treatment. Serious adverse events will be listed. Statistical analyses will be specified in the Statistical Analysis Plan.

Comparative cost-effectiveness analysis will be performed using a health-state transition model, to compare costs and effectiveness between the group treated with TDM-guided dosing and the fixed dosing group. The comparative cost-effectiveness analysis will be performed from both a healthcare and societal perspective, with a lifetime horizon, according to the Dutch guidelines for cost-effectiveness analyses (22).

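### Endpoint 7 judges the toxicity of dose increases by comparing increased with not-increased patients, but tolerability helps decide who is increased, so the contrast is confounded and can understate or reverse a real harm

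*Protocol article*

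**What the plan says.** Section 2.3.4 (Secondary outcomes) lists ten secondary endpoints. The seventh is toxicity in relation to plasma concentration and dose increases. It is defined as AEs in patients below and at or above 435 ng/mL, "and in patients who did and who did not receive a PK-guided dose increase". The same section adds: "Patients medication adherence, toxicity, QoL, cost-effectiveness and alectinib-M4 concentrations will be evaluated in all patients". For response rate, overall survival and intracranial PFS, it instead fixes a comparison of arm A with arm B among patients with a low C_min,SS.

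Section 2.2.1 (Intervention and control group) says who is increased. For a C_min,SS "below the threshold of 435 ng/mL (in arm A) and no or limited toxicity, the patient receives a dose increase". Arm B is sampled on the same schedule, but its results stay blinded and are not acted on.

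Section 2.3.2 (Sample size calculation) sets the expected numbers: "We expect that TDM-guided dosing can improve PFS in 67% of patients with a low exposure". In the other 33% an increase is expected not to be feasible, because of toxicity or because treatment stops at progression.

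Section 2.4 (Data analysis) defines treatment-emergent AEs as those that start or worsen on treatment, and says that "summary tables will be provided by treatment group". It closes that paragraph with "Statistical analyses will be specified in the Statistical Analysis Plan".

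**The concern.** Being in the increased group depends partly on the outcome being studied. A patient must be in arm A, have a low level, still be on treatment when the result arrives, and have little or no toxicity. The not-increased group holds three kinds of patient: arm A patients with low levels who were held back for toxicity or who stopped at progression, arm A patients with adequate levels, and all of arm B. A difference in AEs between the groups mixes the effect of the higher dose with tolerability, exposure and time on treatment.

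Timing adds to this. The article's AE window runs over the whole treatment period, so an AE at the starting dose counts for the increased group if the patient is increased later.

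The consequence matters because section 3 (Discussion) presents the toxicity endpoint as the design's way of keeping safety apart from efficacy, and the trial is meant to inform whether TDM becomes standard care. Efficacy in low-exposure patients gets an arm A versus arm B contrast. Toxicity of the increases gets one in which patients are sorted partly by toxicity. Endpoint 1, feasibility and safety of TDM, does not fill the gap because it is evaluated in arm A only, without a control.

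**Working it through.** **Expected group sizes (article's figures).** The article states no figure for the toxicity contrast, but its group sizes reproduce. 196 patients at 1:1 give 98 per arm. Low exposure per arm: 98 × 0.48 = 47.0, which matches the stated 47 per group.

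- Increased: 47.0 × 0.67 = 31.5, about 32 of 98 in arm A.
- Low and not increased, arm A: 47.0 − 31.5 = 15.5.
- Not low, arm A: 98 − 47.0 = 51.0.
- Arm B: 98.
- All not increased: 15.5 + 51.0 + 98 = 164.5.

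**Illustration (assumed AE rates; the article gives none).** Suppose 70% of patients are tolerant, with a 10% risk of a grade 3 or higher AE, and 30% are intolerant, with a 40% risk. The overall risk is 0.70 × 0.10 + 0.30 × 0.40 = 0.19. Suppose an increase truly multiplies risk by 1.5.

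Case 1, strong selection: all increased patients are tolerant, so 30 of the 33 low-exposure patients per 100 who are not increased are intolerant.

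- Increased: 0.10 × 1.5 = 0.15.
- Low, not increased: (0.30 × 0.40 + 0.03 × 0.10) / 0.33 = 0.373.
- All not increased: (15.5 × 0.373 + 149.0 × 0.19) / 164.5 = 0.207.
- Observed ratio against all not increased: 0.15 / 0.207 = 0.72. The true value is 1.5, so the direction is reversed.

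Case 2, weaker selection: the 70/30 mix is kept, but only half of the 33% are held back for intolerance.

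- Increased: 1.5 × (0.535 × 0.10 + 0.135 × 0.40) / 0.67 = 0.241.
- Low, not increased: (0.165 × 0.40 + 0.165 × 0.10) / 0.33 = 0.25.
- All not increased: (15.5 × 0.25 + 149.0 × 0.19) / 164.5 = 0.196.
- Observed ratio: 0.241 / 0.196 = 1.23. The harm is understated but not reversed.

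**Contrasts by arm, Case 1 rates.**

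- Whole arms: arm A (31.5 × 0.15 + 15.5 × 0.373 + 51.0 × 0.19) / 98 = 0.206; arm B 0.19; ratio 1.08.
- Low exposure only: arm A 0.67 × 0.15 + 0.33 × 0.373 = 0.224; arm B 0.19; ratio 1.18.

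Both point the right way. The true risk difference among increased patients is 0.15 − 0.10 = 0.05. Whole arms show 0.05 × 0.48 × 0.67 = 0.016, about a threefold dilution. The low-exposure contrast shows 0.05 × 0.67 = 0.034.

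**Time on treatment (simulation under assumed inputs).** Inputs: AE hazard 0.02 to 0.10 per month, log-normal variation in susceptibility with SD 0 to 1.5, hazard proportional to concentration to a power of 0 to 1, one increase decision at 1.5 months. Increased versus all not-increased patients:

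- No true effect (72 scenarios): rate ratio per patient-time 0.43 to 0.98, always below 1; ratio of crude AE proportions 0.41 to 1.12.
- True hazard ratio 1.5: rate ratio 0.63 to 1.43, always below 1.5.

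In runs where increased patients stayed on treatment as long as the group at or above 435 ng/mL (median 12.6 × 2.5 = 31.5 months, against 12.6 for low-exposure patients not increased), crude proportions in increased versus low-exposure not-increased patients gave 1.10 to 1.61 with no true effect. That bias runs against the higher dose.

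In the same runs, arm A versus arm B among low-exposure patients gave rate ratios of 0.88 to 1.01 when the truth was 1.0, and 1.11 to 1.47 when it was 1.5. Crude proportions in that contrast were 1.21 to 1.45 with no true effect, so patient-time adjustment is needed there too. These runs counted first AEs from the start of treatment, so they approximate the window proposed below.

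**The case against.** The best defence is that endpoint 7 is a descriptive grouping. No test, effect measure or causal reading is attached to it, and the article refers the statistical detail to an analysis plan that is not shown. Splitting AEs before and after an increase, and using patient-time, are ordinary contents of such a plan. AE tables by randomised arm are also planned. They carry none of this selection, and they describe the harm of the TDM strategy as it would be applied to everyone. Dilution is not bias.

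Much of this stands. The whole-arm tables are valid, and the silence on timing alone would not be a finding. What does not stand is that everything is left open: the article fixes the groups for this endpoint, gives three efficacy endpoints the arm contrast among low-exposure patients, and does not list toxicity with them. A table of low-exposure patients by arm could be built by combining 2.3.4 and 2.4, but the article does not say that it will be.

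Three stronger readings are tempting and are not supported:

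- A reader might infer that the contrast is bound to make the higher doses look safe. It is not: crude proportions can move the other way if increased patients stay on treatment longer.
- A reader might take Case 1's ratio against low-exposure not-increased patients, 0.15 / 0.373 = 0.40, as the size of the bias. The endpoint is evaluated in all patients, and 2.3.2 attributes non-increase to progression as well as toxicity, so that figure uses too narrow a comparator and assigns nearly all non-increase to intolerance.
- A reader might infer that the trial has no sound safety comparison. It has one, by arm.

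**Conclusion.** The point holds in a limited form. Increased versus not increased is confounded by tolerability, exposure and time on treatment, and cannot be read as the toxicity of a dose increase. It can understate a real harm or reverse it. Under the assumed rates, a true ratio of 1.5 appears as about 0.72 with strong selection and about 1.23 with weaker selection. These sizes rest on AE rates and a tolerability mix that are not in the article, and the direction depends on how time on treatment is handled. The expected share increased, about 32 of 98 in arm A, does follow from the article's own figures. The increase rule itself is not in question, and neither is the sample size. For a secondary endpoint that bears on adoption of TDM, and with a cheap remedy, the change should be made.

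**What to change.** State in the analysis plan:

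1. The main analysis of toxicity from dose increases compares arm A with arm B among patients with a first C_min,SS below 435 ng/mL. It counts AEs that start or worsen after that first low sample and reports exposure-adjusted rates with confidence intervals. Both arms are sampled on the same schedule and no TDM increase is made before the first low result, so this start point largely avoids the problem that later levels in arm A are altered by the increase.
2. The whole-arm AE tables stay as planned.
3. Increased versus not increased is labelled descriptive only, with AEs in increased patients split into before and after the increase.

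The cost is wording and one extra cut of the AE tables; AEs and blood-draw times are already recorded. The real downside is precision. With 47 patients per arm and the Case 1 risks, the standard error of the risk difference is √(0.224 × 0.776 / 47 + 0.19 × 0.81 / 47) = 0.083, against an expected difference of 0.034. Whole arms give √(0.206 × 0.794 / 98 + 0.19 × 0.81 / 98) = 0.057 against 0.016. Neither would settle a moderate harm, so the result should be reported as an estimate with its interval.

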Furthermore, Buclin et al. stated in their structured approach to implement TDM, that cost-effectiveness is likely to be confirmed, given the high prices of targeted anti-cancer agents (i.e. alectinib) and TDM requires only a minor improvement in efficacy to be cost-effective (27). However, evidence for the cost-effectiveness of TDM of targeted anticancer agents is lacking. Therefore, QoL and cost-effectiveness are included in the ADAPT ALEC protocol, which is an important strength of this study design and will help decision making in terms of implementation of TDM. We expect a longer PFS when comparing the subpopulations with low exposure (C_min,SS_ < 435 ng/mL) in TDM and fixed dosing group, while we expect the QoL to be the same in both groups. It is hypothesized that this will result in acceptable costs for gain in life years without being at expense of QoL. In clinical practice (not in this trial), TDM can also lead to a decreased dose in case of a high exposure. This will be captured in a hypothetical scenario, based on data in the trial (decreased dose in case of toxicities) and expert opinion. Taken this into account, it could mean that the incremental cost-effectiveness ratio will be more favorable.

Besides secondary endpoints on efficacy and safety, other valuable data will be collected, for instance alectinib-M4 concentrations. Alectinib-M4 is the major active metabolite of alectinib and is formed by cytochrome P450 3A4 (CYP3A4), which accounts for approximately 40% of alectinib’s metabolism (12). Alectinib and its metabolite M4 are equally active. In case of using CYP3A4 modulators, the ratio of alectinib and M4 concentrations will change without a meaningful change in combined exposure of alectinib and M4. Therefore, in current clinical practice no dose adaptations are recommended in case of concomitant administration of CYP3A4 modulators. When performing TDM of only alectinib without measuring M4, caution is needed that combined exposure is under- or overestimated. The effect of CYP3A4 modulators is not studied in this trial, but alectinib-M4 exposure relative to alectinib plasma concentrations will be an important component to explore as limited data regarding alectinib-M4 exposure is available.

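### QoL is assigned to all patients while efficacy is compared only in low-exposure patients, so the stated QoL population does not match the claim of longer PFS at no cost in QoL

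*Protocol article*

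**What the plan says.** The article's Primary outcome section (2.3.3) compares PFS between arms in patients with C_min,SS below 435 ng/mL. Secondary outcomes (2.3.4) names a population for each further endpoint. ORR, OS and intracranial PFS are compared between arms in that same subgroup. For QoL the text is: "Patients medication adherence, toxicity, QoL, cost-effectiveness and alectinib-M4 concentrations will be evaluated in all patients".

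Toxicity stands in that sentence too, but its own definition (endpoint 7) breaks it down by exposure and by whether a PK-guided increase was received. The QoL definition (endpoint 8) lists the questionnaires and gives no breakdown.

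The Discussion (section 3) reads the two results together. It expects longer PFS in the low-exposure subpopulations of the two arms, "while we expect the QoL to be the same in both groups", and hypothesises "acceptable costs for gain in life years without being at expense of QoL".

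The shares that matter are in Sample size calculation (2.3.2): "It is expected that 48% of the patients treated with alectinib in our study will be underdosed"; "We expect that TDM-guided dosing can improve PFS in 67% of patients with a low exposure"; and "In the remaining 33% of patients, TDM-guided dose increases are expected not to be feasible due to toxicity or treatment discontinuation".

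**The concern.** Under Intervention and control group (2.2.1), a TDM-driven increase can occur only in arm A and only after a concentration below 435 ng/mL. The Discussion adds that TDM-driven reductions for high exposure are not part of this trial. Patients who stay at or above the threshold therefore have no TDM-driven dose change in either arm, and they add noise but no signal to a between-arm QoL comparison.

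The benefit would be read in the subgroup that TDM can affect, and the QoL price averaged over a population at least half of which TDM cannot affect. A moderate loss among patients given higher doses could go unseen while the trial reports a PFS gain without QoL cost. QoL was added at the patient federation's recommendation and supports the cost-effectiveness argument, so the matter is not incidental.

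**Working it through.** **The plan's own figures.** The article states: "With 67 events, a power of 80% will be obtained to detect this HR of 2 using the log-rank test", "assuming a two-sided significance level of 5"%.

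- Events (Schoenfeld): 4 × (1.960 + 0.842)² / (ln 2)² = 65.3, so 66; with 67 events power is 81%.
- Event probability, exponential survival, accrual A = 48 and follow-up F = 12 months, λ = ln 2 / median: 1 − [exp(−λF) − exp(−λ(A+F))] / (λA) = 0.818 for a median of 12.6 and 0.601 for 25.2; mean 0.710.
- Patients: 67 / 0.710 = 94.4, stated as 94 (47 per arm). Recruitment: 94 / 0.48 = 195.8, stated as 196 (98 per arm at 1:1).

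The stated design reproduces, so 98 and 47 per arm are used below.

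**Share of arm A with a TDM-driven increase.**

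- Lower figure, only the 67% who benefit are increased: 0.48 × 0.67 = 0.32; no workable increase in 1 − 0.32 = 68%.
- Upper figure, all low-exposure patients are increased and the 33% then fail: 0.48; no increase in 52%.

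The range is needed because toxicity is one of the reasons given for the 33%, and some of those patients may be increased first.

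**Dilution in the all-patient comparison.**

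- Relative to patients given an increase: 1 / 0.48 = 2.1 to 1 / 0.32 = 3.1.
- Relative to the low-exposure subgroup: 1 / 0.48 = 2.08.
- The same in signal-to-noise, allowing for the larger sample: 2.08 × √(47/98) = 1.44.

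**Power.** The article gives no QoL effect size or SD, so these are assumptions: loss of 10 or 15 points on a 0–100 scale, SD 20 or 25, loss confined to the 67%, complete data, two-sided 5%. Power = Φ(effect / (SD × √(2/n)) − 1.96).

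| Loss in increased patients | All patients (n = 98 per arm) | Low exposure (n = 47 per arm) |
|---|---|---|
| 10 points | difference 3.2; power 14–20% | difference 6.7; power 25–37% |
| 15 points | difference 4.8; power 27–39% | difference 10.05; power 50–68% |

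Example, 10 points and SD 20: 3.2 / (20 × √(2/98)) = 1.13, and Φ(1.13 − 1.96) = 20%. For the subgroup: 6.7 / (20 × √(2/47)) = 1.62, and Φ(1.62 − 1.96) = 37%.

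**Sensitivity.** If all low-exposure patients lose 0.5 SD, power is 39% in all patients and 68% in the subgroup. If only the 67% are affected, losses of 0.8 and 1.0 SD give 44% and 62% in all patients, against 74% and 90% in the subgroup. The subgroup has more power in every case, with half the patients.

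**The case against.** Several points on the other side stand.

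- Evaluating QoL in all patients says who is assessed and does not exclude a subgroup contrast: toxicity is in the same sentence and is split. The SAP, which is not shown, may contain a QoL contrast. What remains is that the article assigns a comparison population endpoint by endpoint, and the one it gives QoL is not the one in which the Discussion frames its claim.
- The Discussion can be read as already meaning QoL in the low-exposure groups. That shows the intended question and makes the mismatch with Secondary outcomes plainer.
- The all-patient comparison is legitimate. It keeps the full randomised comparison, answers whether offering TDM changes QoL across those treated, and matches the population stated for cost-effectiveness. The low-exposure subgroup, by contrast, is defined by samples taken after randomisation.
- Harm from dose increases is not hidden: toxicity by dose increase and the safety of TDM in arm A are endpoints.

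A reader might infer more than the documents support:

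- *That a finding of equal QoL is close to guaranteed.* No text makes a non-significant test the criterion. On the assumptions above, a non-significant all-patient result has a chance of 80–90% for losses of 0.3–0.5 SD, but only 38–56% for 0.8–1.0 SD.
- *That dilution is threefold.* That holds only against patients with a workable increase, at the top of the range; against the efficacy population it is 2.1-fold.
- *That two thirds of patients are dosed identically in both arms.* Only the 52% who never fall below the threshold are sure to trigger no increase.
- *That the PFS benefit is read undiluted.* The primary comparison includes the 33% with an assumed HR of 1, which brings 2.5 down to 0.67 × 2.5 + 0.33 × 1 = 2.0.

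**Conclusion.** The point holds as a mismatch between the stated QoL population and the claim made for it. Against the subgroup used for efficacy, the all-patient comparison shrinks a QoL effect of dose increases 2.1-fold and weakens signal-to-noise 1.44-fold. For a moderate loss both analyses are weak, the all-patient one more so, and a non-significant result in either would not show that QoL is unchanged.

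The dilution figures rest on the article's 48% and 67%. The power figures also rest on the assumed losses and SDs, complete data, and an effect only in patients with a workable increase; they illustrate direction and rough size. The matter is worth correcting, but does not touch the primary analysis.

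**What to change.** In Secondary outcomes, add a between-arm QoL comparison (QLQ-C30, LC13, EQ-5D-5L) in the same C_min,SS below 435 ng/mL subgroup as the primary endpoint, using assessments from the first low sample onward in both arms. Arm B is sampled on the same schedule with results blinded, so the starting point can be defined alike. Keep the all-patient comparison alongside it for the policy and cost-effectiveness question. Base any statement that the PFS gain is not at the expense of QoL on the 95% confidence interval of the subgroup difference, so that the largest loss not excluded is visible, and not on a non-significant test.

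The cost is a change of wording and one added analysis of data already collected. The interval is wider: at SD 20 to 25 its half-width is 1.96 × SD × √(2/47) = 8.1 to 10.1 points, against 5.6 to 7.0 with 98 per arm. The subgroup rests on post-randomisation samples, as it does for the primary endpoint, and the report should say so.
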